### Statistical analyses

The statistical analysis of the primary outcome, effectiveness of the intervention for weight loss, will be carried out on the basis of intention-to-treat (ITT). That is, after randomisation, participants will be analysed according to their allocated intervention group. We will endeavour to obtain full follow-up data on every participant to allow full ITT analysis. A linear regression, predicting weight at 8 weeks’ follow-up while adjusting for baseline weight and GP practice, will assess the effect of condition.^37^ We will assess the sensitivity of the analysis to different assumptions about missing data using a variety of imputation methods, including baseline observation carried forward analysis and an analysis of participants completing follow-up. A final analysis will impute the last home-measured weight for people who did not attend the final follow-up. All tests will be done at a 5% two-sided significance level.

Secondary outcomes will be analysed in several ways. Adherence rates will be assessed and compared between the experimental and control condition. Moderator analyses will assess the effect of adherence, highest educational qualification, liking of weighing at baseline, and overall intervention rating at follow-up (only intervention condition) on weight change.

Further exploratory analyses may be added post-hoc based on preliminary findings. The statistical analysis plan can be found in online supplementary appendix 2.

10.1136/bmjopen-2019-031572.supp2Supplementary data

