What	*Self-weighing*: Participants will be instructed to weigh themselves daily using simple digital body scales (Etekcity Corporation, California). They will be asked to weigh themselves in a similar state every day, ideally first thing in the morning and without clothes. *Weight tracking:* Participants will be asked to download the free app “Weight Loss Tracker, BMI” by aktiWir GmbH on their smartphone and use it on a daily basis to record their weight measurements. They will be asked to submit a backup of their data to the research team every week. *Action* *p* *lanning:* Participants will receive a daily questionnaire helping them to plan a weight loss action. The questionnaire will start by asking participants to enter their morning weight. At the beginning of first week, they will then be asked to choose a category of actions, and they will be able to choose one of the actions within this category per day for the rest of the week. There are seven categories in total, five covering diet-related actions and two covering physical activity-related actions. Participants will be asked to specify for each action how, when and where they are going to perform it, and which cues they are going to use. They will also be prompted to think about how to overcome potential barriers. At the start of weeks 2 through 8, participants will be encouraged to try out a new category of actions. We will additionally ask participants on a weekly basis to commit to continuing some of the actions they tried out in previous weeks. In order to help participants to maintain an overview of the actions they performed so far, we will provide them with a non-digital action plan diary. *Report email:* Once a week, participants will receive an email from the research team, informing them about their trend weight change for the last week. This trend weight change consists of the slope of a trend line fitted across all measurements of the week, multiplied by the number of days covered by the measurements. The weight measurements used to create these reports will be taken from the daily action planning questionnaires. *Reflection and* *a* *ction* *e* *valuation:* In the weekly report email, participants will receive a link to the reflection and action evaluation questionnaire. This questionnaire prompts participants to think about why their weight has changed as it has. They are further asked to evaluate the group of actions they performed across the week, including whether they found them useful and whether they would repeat them. On the basis of this evaluation, participants will be able to decide which actions they want to continue doing in the next weeks, and which ones to drop. Using this method of self-experimentation, participants will be able to try and test different weight-loss strategies and identify the ones that are effective and sustainable for them.	Self-weigh every morning in a similar state, using smart scales (BodyTrace, New York).

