#### Physical measurements

Participants’ height will be measured at baseline to the nearest 0.1 cm using a stadiometer. Weight will be measured both at baseline and follow-up using a digital scale (SC-240 MA, Tanita Japan). Weight will be recorded to the nearest 0.1 kg.

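### Imputing an unconverted home weight for a missing clinic weight can put an arm-dependent scale and clothing offset into one sensitivity analysis

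*Protocol article*

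**What the plan says.** All of this is in the protocol article.

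- **Main model (Statistical analyses).** "A linear regression, predicting weight at 8 weeks’ follow-up while adjusting for baseline weight and GP practice, will assess the effect of condition".
- **Missing data (Statistical analyses).** "We will assess the sensitivity of the analysis to different assumptions about missing data using a variety of imputation methods". Baseline observation carried forward and a completers' analysis are named, followed by: "A final analysis will impute the last home-measured weight for people who did not attend the final follow-up".
- **Clinic weight (Physical measurements).** "Weight will be measured both at baseline and follow-up using a digital scale (SC-240 MA, Tanita Japan"). No clothing rule for the visits is given.
- **Home weight, intervention (Table 1, What).** "Participants will be instructed to weigh themselves daily using simple digital body scales (Etekcity Corporation, California"). The next sentence reads: "They will be asked to weigh themselves in a similar state every day, ideally first thing in the morning and without clothes". Participants enter these weights themselves, in the app or the daily questionnaire.
- **Home weight, control (Table 1, What).** "Self-weigh every morning in a similar state, using smart scales (BodyTrace, New York"). The Control section adds that no further instruction is given. Readings reach the server automatically.

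**The concern.** For a participant who attends, baseline and follow-up are read on the same clinic scale model. For a non-attender under the home-weight rule, baseline is a clinic reading and follow-up is a home reading. The gap between the two settings (scale calibration, clothing, time of day) is then booked as weight change. Adjusting for baseline weight cannot remove it, because it enters only at follow-up and only for those imputed.

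A shared gap would largely cancel between arms. Here the home device, the way readings are captured and the stated clothing instruction all differ by arm, so there is no ground for assuming that it cancels.

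Among the methods the article names, this is the only one that uses non-attenders' own later weights, so readers will give it weight when judging whether the result survives drop-out. If it carries an offset that depends on arm, its agreement or disagreement with the main result could be a measurement artefact.

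**Working it through.** **Inputs from the protocol article.** Recruitment of 100, allocated 1:1, so 50 per arm; target difference 1.5 kg; SD of weight change 2.13 kg; 20% drop-out; two-sided 5% test (Sample size; Randomisation and blinding; Statistical analyses).

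**Inputs that are assumptions.** The home-versus-clinic offsets, and any split of drop-out between arms. The documents give neither, so ranges are shown.

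**The plan's own figure.** The article gives no figure for the offset. Its power statement, used here only for scale, comes out close. With 40 completers per arm, 1.5 / (2.13 × √(2/40)) = 3.149; 3.149 − 1.960 = 1.189; power = 88.3%, against 90% stated.

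**Bias formula.** Let d be the share imputed in an arm and o the clinic-minus-home offset (positive when the home reading is lighter). Each imputed follow-up weight is too low by o. With d and o indexed by arm (I intervention, C control), the bias in favour of the intervention is

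d_I × o_I − d_C × o_C.

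| Imputed, I / C | Offset (kg), I / C | Bias towards intervention (kg) | Share of 1.5 kg |
|---|---|---|---|
| 20% / 20% | 1.0 / 1.0 | 0.20 − 0.20 = 0 | 0% |
| 20% / 20% | 1.0 / 0.5 | 0.20 − 0.10 = 0.10 | 7% |
| 20% / 20% | 1.0 / 0 | 0.20 | 13% |
| 20% / 20% | 1.5 / 0 | 0.30 | 20% |
| 20% / 20% | 2.0 / 0 | 0.40 | 27% |
| 30% / 10% | 1.0 / 1.0 | 0.30 − 0.10 = 0.20 | 13% |
| 20% / 20% | 0.5 / 1.0 | 0.10 − 0.20 = −0.10 | −7% |
| 15% / 25% | 1.0 / 1.0 | 0.15 − 0.25 = −0.10 | −7% |

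The first row shows that equal offsets with equal drop-out do no harm. The last two show the sign reversing.

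**Type I error.** A simulation with no true effect used 50 per arm, SD of change 2.13 kg, regression on arm and baseline weight (no practice term) and 6,000 runs. Rejection rates with unconverted home weights, 20% imputed per arm:

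- offsets 1.0 / 1.0 kg: 4.4%
- offsets 1.0 / 0 kg: 7.3%
- offsets 1.5 / 0 kg: 10.6%

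A hand check of the 1.5 / 0 case: the offset adds 0.2 × 0.8 × 1.5² = 0.36 to the intervention-arm variance, so the average variance is 2.13² + 0.18 = 4.717. The SE is √(4.717 × 2/50) = 0.434 kg, and 0.30 / 0.434 = 0.69. The chance that |Z| exceeds 1.96 with that shift is about 0.102 + 0.004 = 10.6%, which agrees.

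**After the fix.** Write a home reading as the clinic-equivalent weight minus o. Then clinic baseline + (last home − first home) = baseline + (last − o) − (first − o), and a constant o cancels in each participant. With the offset removed exactly, the simulated bias was within 0.01 kg of zero and the type I error was 4.7% to 5.2% in every scenario run.

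**The case against.** **The analysis plan may already deal with this.** The article refers to a statistical analysis plan in appendix 2, which is not at hand, and a conversion may be specified there. That limits what can be claimed: no conversion appears in the rule as the article states it. It does not dispose of the point, because the article names the value to be imputed, and taking that literally produces the artefact.

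**Only one sensitivity analysis is touched.** This stands. The main regression uses clinic weights at both visits, and neither baseline observation carried forward nor the completers' analysis uses home readings. A reader might infer that the trial's main result is biased towards the intervention; the documents do not support that.

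**The direction is not established.** This also stands. A reader might infer conflicting clothing rules and therefore a built-in advantage for the intervention. The documents show less. The intervention arm is told "ideally first thing in the morning and without clothes", while the control arm has no clothing instruction rather than a contrary one. Both arms weigh in the morning in a consistent state, so any fasting component is largely shared. The clinic clothing rule is not stated, and the errors of the three scales are unknown in sign.

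**The size rests on assumed offsets.** True. Offsets of 1.5 versus 0 kg are an extreme case, since they give controls no home-versus-clinic gap at all. With 1.5 / 1.0 kg, the bias is 0.2 × 0.5 = 0.10 kg and simulated rejection is 5.7%. The 20% is a planning allowance, and not every non-attender will have a usable home reading. At 10% imputed, even 1.5 / 0 kg gives about 0.10 × 1.5 = 0.15 kg and 6.8% rejection.

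**Conclusion.** The point holds as a weakness of one sensitivity analysis, of minor to moderate importance. Used unconverted, home weights let a home-versus-clinic offset pass as weight change in non-attenders, and the documented differences between arms in device and clothing instruction mean that it need not cancel.

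With 20% imputed per arm, the bias is 0.2 times the difference in offset between arms: 0.1 kg for a 0.5 kg difference and 0.4 kg for 2 kg, or 7% to 27% of the 1.5 kg target. The extreme 1.5 versus 0 kg case gives about 0.30 kg and a type I error of 10% to 11%. All of this depends on offsets that the documents do not report.

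A bias towards the intervention is the more natural guess from the clothing instruction, but it is an inference. A larger offset or more drop-out in the control arm would reverse it.

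**What to change.** In this sensitivity analysis, replace the raw home weight by one of the following, and state which:

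1. clinic baseline weight + (last home weight − first home weight on the same scale); or
2. the last home weight calibrated to the clinic scale, with the calibration estimated separately by arm in participants who attended follow-up.

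Add a stated fallback for non-attenders who have no early home reading.

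The cost is a sentence or two of text and a few lines of code, since daily home weights are already collected in both arms. Option 1 assumes little weight change between the baseline visit and the first home reading, and it carries the day-to-day noise of two readings. Option 2 assumes that the offset in attenders also applies to non-attenders. Neither requires a change to the control arm's weighing instruction or to how the trial is run.

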### Randomisation and blinding

All eligible participants will be randomised with an allocation ratio of 1:1 to the intervention or control group. A randomisation sequence, stratified by GP and using block randomisation with randomly varying block sizes of 2 and 4 will be generated using a computer algorithm. Allocations will be concealed in numbered, sealed, opaque envelopes by an independent researcher in the department and handed to the researcher who will conduct the baseline visits.

Due to the nature of this trial, it will be difficult to blind participants to the treatment allocation. We will aim to make it as opaque as possible by presenting daily weighing as an intervention to control group participants, as done in previous trials.^29^ The researchers conducting baseline and follow-up will perform data analysis, and will not be blinded to treatment allocation. The primary outcome, weight change, will be measured objectively. Adherence to self-regulation steps will be measured objectively through the frequency of weight logs and completed questionnaires in control and intervention group. The evaluations of treatment components in the final questionnaire will be measured without researchers’ input and analysed quantitatively. Blinding of the researcher who conducts and analyses the semi-structured interviews with intervention group participants will not be possible.

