### Intervention and control

#### Intervention

Participants will be asked to weigh themselves every morning after waking using standard body scales (Etekcity, California, USA) provided to them. In addition, they will be prompted to complete tasks which speak to the different steps of the self-regulation process, including (1) contextualising the weight measurement, (2) reflecting on behaviour and (3) planning weight loss actions. The individual tasks and their development are described in more detail below. Input from members of the public was sought at several stages of the intervention development.

Contextualising: In the think-aloud study participants struggled memorising daily measurements and keeping an overview of their weight loss progress, which impeded their ability to use weight measurements as constructive feedback. Participants stated they would have benefited from a weight tracking tool. Therefore, to support participants in contextualising their weight measurements, we will encourage them to use the app ‘Weight Loss Tracker, BMI’ by aktiWir GmbH. Research shows that digital tracking devices can significantly increase adherence to self-monitoring,^30 31^ perhaps because the visualisation of progress and feedback on weight loss success provides motivation and keeps users on track with their goals.^32^

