#### Control

Participants in the control group will be instructed to self-weigh daily and see what daily weighing motivates them to do. They will not receive any further instructions. By using this comparator group, we want to test whether the self-regulation process can enhance self-weighing to be an effective weight loss tool. Participants will receive smart scales (BodyTrace, New York) which are equipped with a SIM card and automatically transfer measurements to a secure server via the 3G/4G network. This will allow us to assess adherence to daily weighing in the control group.

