#### Process evaluation measures

##### Adherence measures

For the control group, adherence to daily weighing will be measured by calculating the proportion of days for which we have a recorded weight measurement on the BodyTrace server.

For the intervention group, adherence to daily weighing will be assessed by calculating the proportion of days for which a weight was recorded in the weight tracking app or in the daily action planning questionnaire. Adherence to weight-tracking will be calculated as the proportion of days for which a weight measurement was recorded in the app. Adherence to action planning and reflection will be measured by calculating the proportion of days on which the respective questionnaires were completed. An overall adherence score will be calculated averaging adherence rates across all intervention components.

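### The between-arm comparison of daily-weighing adherence mixes any true difference with a difference in capture method: automatic transmission in controls, participant entry in the intervention arm

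*Protocol article*

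**What the plan says.** The Statistical analyses section of the protocol article states that "Adherence rates will be assessed and compared between the experimental and control condition", shortly after setting a general rule: "All tests will be done at a 5% two-sided significance level". Adherence is listed first among the secondary (process evaluation) outcomes.

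The Adherence measures section defines daily weighing separately for each arm:

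- **Control:** the "proportion of days for which we have a recorded weight measurement on the BodyTrace server". The Control section says these scales are "equipped with a SIM card and automatically transfer measurements to a secure server via the 3G/4G network".
- **Intervention:** "the proportion of days for which a weight was recorded in the weight tracking app or in the daily action planning questionnaire". The Intervention section has this arm weighing "using standard body scales (Etekcity, California, USA) provided to them", and no automatic transfer is described for that scale. Table 1 explains that the daily questionnaire opens by asking for the morning weight and that participants send in app backups weekly.

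Table 2 marks weight tracking, the daily questionnaire and the weekly questionnaire as intervention-only. The Randomisation and blinding section says: "Adherence to self-regulation steps will be measured objectively through the frequency of weight logs and completed questionnaires in control and intervention group".

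**The concern.** Only one adherence component can be compared between arms, namely daily weighing, and for that component arm and capture method coincide completely. An intervention participant who steps on the scale but enters nothing is counted as not having weighed; a control who does the same is counted, provided the transmission succeeds. Conversely, a number entered without weighing counts in the intervention arm and has no counterpart in controls.

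No later analysis can separate the two effects, because no participant is measured both ways. A reader of the results would naturally use this comparison to ask whether the intervention changed how often people weighed, and hence to help explain any weight difference. The same asymmetry enters the moderator analysis if adherence is pooled over arms. The statement in Randomisation and blinding that adherence is measured objectively in both arms hides the problem, because it comes directly after the admission that the researchers are not blinded.

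**Working it through.** The documents give no expected adherence rate, SD or power for this comparison, so there is no planned figure to reproduce. What follows is an illustration.

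**Model.** Let p be the true proportion of days with a weighing, the same in both arms. Let l be the chance that an intervention weighing is entered by either route, f the chance that a weight is entered on a day without weighing, and c the chance that a control weighing reaches the server.

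- Recorded rate, intervention: p·l + (1 − p)·f
- Recorded rate, control: p·c
- Artefact (intervention minus control): p·(l − c) + (1 − p)·f

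Apart from chance cancellation, the artefact is zero only if f = 0 and l = c.

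**Inputs.** From the documents: 100 participants randomised 1:1, so 50 per arm, and a two-sided 5% level. Assumed: p = 85%, between-person SD of 25 points, f = 0, c = 1.

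**Rejection rate with no true difference.** The standard error is 25 × √(2/50) = 5.0 points. The two-sample t-test has 98 degrees of freedom and a critical value of 1.984. The noncentrality is the artefact divided by 5.0.

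| Share of weighings logged (l) | Artefact, 85 × (l − 1) | Noncentrality (absolute) | Rejection rate (nominal 5%) | Same, 40 per arm |
|---|---|---|---|---|
| 95% | −4.25 points | 0.85 | 13.4% | 11.7% |
| 90% | −8.5 points | 1.70 | 39.1% | 32.4% |
| 85% | −12.75 points | 2.55 | 71.4% | 61.5% |

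The last column applies the protocol's 20% drop-out allowance (50 × 0.8 = 40). At l = 90% and 50 per arm, the rejection rate is 55.7% with an SD of 20 and 28.9% with an SD of 30.

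**Other inputs.** With p = 80%, SD 20 points, c = 1, 50 per arm and a normal approximation, l = 95%, 90% or 80% gives −4, −8 or −16 points and rejection rates of 17%, 52% and 98%.

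**Direction.** The sign is not fixed. With p = 80%, full logging (l = 1) and 10% of control weighings lost in transmission (c = 0.90), the artefact is 80 × (1 − 0.90) = +8 points, and the rejection rate is again 52%. With f = 0 and p from 70% to 90%, l from 80% to 100% and c from 90% to 100%, the artefact runs from 90 × (0.80 − 1.00) = −18 points to 90 × (1.00 − 0.90) = +9 points. Entries made without weighing add a further positive term: at p = 85% and f = 10%, it is 15 × 0.10 = +1.5 points.

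**The case against.** Several counter-arguments have force.

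- **Under-recording may be small.** Either of two routes counts in the intervention arm, and a questionnaire emailed every morning begins by asking for the weight. That could bring l close to 1. It does not make the two definitions equal, and the prompt that limits missed entries also invites entries without a weighing.
- **Most of what is logged really is objective.** Weight tracking, action planning and reflection are themselves acts of recording, so counting records measures them directly. This stands. The word is wrong only for daily weighing in the intervention arm.
- **This is a process outcome in a proof-of-concept trial.** That also stands and limits the weight of the point. The primary outcome is weight measured by the research team on the same scale model in both arms.
- **The analysis plan is in an appendix that is not shown.** It may specify the test or add a caveat. The article says only that rates are compared, and its 5% rule covers all tests, so a test is the natural reading but not a certainty. An analysis plan cannot supply common measurements that the design does not collect.

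A reader might infer that the observed difference will merely reflect the method, or that the intervention arm will necessarily look worse. The documents support neither: a true difference may also be present, and the direction of the artefact is open. Nor do they say that controls are told their readings are transmitted, so no argument about differing awareness can be built on them.

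**Conclusion.** The point holds as a limited one. Daily-weighing adherence is measured on a different basis in each arm, so the planned comparison estimates a true difference plus an artefact whose size and sign cannot be recovered from the data. Under the assumed inputs, modest under-logging of 5% to 15% would produce spurious deficits of about 4 to 13 points and raise the chance of a significant result from 5% to between 13% and 71%. These figures show how sensitive the comparison is; they do not forecast what this trial will see. They rest on assumed values for true weighing, SD and logging, on complete capture in controls, and on no entries without weighing. A very large observed difference could still be informative, but a moderate one could not be interpreted. The primary analysis is not touched.

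**What to change.** At little cost:

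1. Drop the between-arm significance test of daily-weighing adherence. Report each arm's rate descriptively, stating beside it how weighings were captured.
2. Do not pool adherence over arms in the moderator analysis; examine it within arm.
3. In Randomisation and blinding, describe daily weighing in the intervention arm as self-entered, and say that the questionnaires apply to that arm only. The description as objective can stay for weight tracking, action planning and reflection, where the record is itself the behaviour.

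The cost is one secondary test given up and a few lines of text.

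If budget allows, issue the same transmitting scale to both arms and apply the server rule to both for this comparison, keeping app and questionnaire records for the intervention-only components. This costs additional transmitting scales, which participants return at follow-up. It removes the difference in capture method while keeping the comparison.

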#### Follow-up

The aim of the follow-up appointment is to assess the outcomes of the trial. The research team will email participants in advance to remind them of the meeting. In the intervention group, this email will also contain a final questionnaire, asking participants about the usefulness of each of the intervention components and an overall rating of the intervention.

The appointment will be scheduled at a local venue and conducted by a member of the research team. Participants will be asked to return the body scales. The researcher will measure participants’ weight.

Twenty participants in the intervention group will be invited to participate in a semi-structured interview at the end of the follow-up meeting. The interviewees will be sampled by the lead researcher with the aim to reflect different levels of adherence, weight change and responses to the final questionnaire. Participants will be asked about their experiences with self-weighing, their liking of the intervention components and perceived barriers to engaging with the intervention. Interviews will be recorded, transcribed and analysed. A study flow chart is displayed in figure 1.

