#### Secondary outcomes (process evaluation)

Adherence to self-regulation steps, assessed through weight records and daily action planning/weekly evaluation questionnaires.Test moderators of effectiveness: adherence measures, highest educational qualification, liking of weighing at baseline, overall rating of intervention in final questionnaire.Perceived effectiveness of intervention and liking of intervention features based on final questionnaire and follow-up interviews.Barriers and unmet needs for successful weight loss, assessed in follow-up interviews.

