### Measurements

A schedule of measurements can be found in table 2.

**Table 2 T2:** Schedule of measurements

	Screening	Baseline visit	Intervention period	Completion email	Follow-up visit (after 8 weeks)
Length	10 min	Up to 1 hour	10 min per day	5 min	up to 45 min
Who conducts	Research team	Research team	Participants	Research team	Research team
Eligibility assessment	☑	☑ (BMI)			
Enrolment		☑			
Baseline questionnaire		☑			
Weight		☑	☑		☑
Height		☑			
Allocation		☑			
Weight tracking (only intervention)			☑		
Daily questionnaire (only intervention)			☑		
Weekly report and questionnaire (only intervention)			☑		
Final questionnaire (only intervention)				☑	
Semistructured interview (20 participants in intervention group)					☑

BMI, body mass index.

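### Adherence and the end-of-programme rating are listed as moderators of effectiveness but arise after randomisation, and for the two baseline variables the article's wording describes a prognostic effect unless an interaction is fitted

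*Protocol article*

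**What the plan says.** Under Secondary outcomes (process evaluation), the protocol article gives the aim as: "Test moderators of effectiveness: adherence measures, highest educational qualification, liking of weighing at baseline, overall rating of intervention in final questionnaire". Effectiveness here means the difference between the intervention and daily weighing alone.

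Under Statistical analyses, the matching sentence begins "Moderator analyses will assess the effect of adherence, highest educational qualification, liking of weighing at baseline, and overall intervention rating at follow-up". Read from education to its end, it shows the outcome and the restriction on the rating: "highest educational qualification, liking of weighing at baseline, and overall intervention rating at follow-up (only intervention condition) on weight change". No model is written out for it. The section refers the reader to a statistical analysis plan in a supplementary appendix, which is not at hand.

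Three other places bear on the variables themselves:

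- Adherence measures, control arm: "For the control group, adherence to daily weighing will be measured by calculating the proportion of days" with a weight on the scale's server. Only daily weighing is measured there.
- Adherence measures, intervention arm: weighing, app tracking, action planning and reflection are each measured, and "An overall adherence score will be calculated averaging adherence rates across all intervention components".
- Follow-up: the reminder email goes to everyone, but "In the intervention group, this email will also contain a final questionnaire", which holds the overall rating. The schedule in Table 2 likewise marks this questionnaire as intervention-only and places it in the completion email.

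**The concern.** A moderator of effectiveness is a characteristic across whose levels the intervention-minus-control difference varies. It must be defined in both arms and must not itself be a result of allocation or of the outcome. Adherence and the rating fail this test.

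There are two ways to be misled. First, people who are losing weight may keep weighing, keep completing the questionnaires and rate the programme highly because it is working. More motivated people may do all of these things and also lose more weight. Presenting such associations as moderation would tell readers who benefits when the data cannot show it. Second, for education and liking of weighing, a variable that predicts weight loss equally in both arms would look like a moderator if its effect on weight change were the quantity tested.

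**Working it through.** **1. Can each variable be a moderator?** Write D(v) for the mean weight change in the intervention arm minus that in the control arm, among people with V = v. Moderation by V is D(1) − D(0). A prognostic effect is the difference in mean weight change between V = 1 and V = 0, averaged over arms.

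- *Overall rating.* It has no control-arm value, so D(v) cannot be formed. Only a relation within one arm can be estimated. By the time they rate, participants have been asked to weigh daily and log weights in an app, and have been sent weekly weight-trend emails. They therefore largely know their result.
- *Overall adherence score.* It averages components that only the intervention arm has, so D(v) cannot be formed here either.
- *Adherence to daily weighing.* It is measured in both arms as the proportion of days with a recorded weight, though from different sources: automatic transmission in the control arm, app or questionnaire entries in the intervention arm. D(v) can be computed, but people with equal adherence in the two arms are no longer groups formed by randomisation, because allocation and progress can both change adherence.
- *Education and baseline liking of weighing.* Both precede randomisation and exist in both arms, so D(1) − D(0) is well defined and needs a condition-by-variable term.

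**2. Inputs for the two baseline variables.** From Sample size: 100 recruited, 20% drop-out, SD 2.13 kg, target difference 1.5 kg, 90% power, 5% type I error. Statistical analyses makes all tests two-sided. Allocation is 1:1, so 100 × 0.8 = 80 completers, 40 per arm. The moderator analysis has no figure of its own. The nearest stated figure is the power of the primary comparison:

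SE = 2.13 × √(2/40) = 0.476 kg; power = Φ(1.5/0.476 − 1.96) = Φ(1.19) = 0.883, close to the stated 90%.

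**3. If an effect on weight change were read as moderation.** Assume a binary variable split 50:50 (not in the documents) that shifts weight change equally in both arms, so the true interaction is zero. The standard error is again 0.476 kg, and the chance of significance is Φ(shift/0.476 − 1.96):

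| Assumed shift | Chance of a significant result |
|---|---|
| 0.5 kg | 18% |
| 1.0 kg | 56% |
| 1.5 kg | 88% |

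The nominal rate for a variable that moderates nothing is 5%.

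A simulation with other assumed values shows that the error runs both ways. It used 40 per arm, a standard normal variable, residual SD 2.0 kg, a 1.5 kg treatment effect and 4,000 runs.

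- A purely prognostic variable (0.8 kg per SD) was significant on weight change in 93% of runs and on the interaction in 4%.
- A pure moderator (interaction 1.6 kg per SD, no average effect on weight change) was significant on weight change in 7% and on the interaction in 92%.

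**4. What the interaction test can detect.** With 20 per cell, SE = 2.13 × √(4/20) = 0.953 kg.

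| True interaction | Power, 80 completers |
|---|---|
| 0.75 kg | 12% |
| 1.5 kg | 35% |
| 3.0 kg | 88% |

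Detectable with 80% power: (1.96 + 0.84) × 0.953 = 2.67 kg. With all 100 followed up, SE = 2.13 × √(4/25) = 0.852 kg, power for 1.5 kg is 42%, and the detectable interaction is 2.39 kg.

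**The case against.** The strongest reply is that the article is a condensed account. It names moderation as the target in both places, gives no model for it, and defers to an analysis plan that may well contain the interaction terms. This stands for education and liking of weighing. A reader might infer from the Statistical analyses sentence that only main effects will be fitted, and hence that the trial cannot identify any moderator. The documents do not support that: the sentence is loose, not a statement that the interaction is left out, and these two variables are valid candidates. The percentages in step 3 of the working therefore apply only if a main-effect test is run and reported as moderation, and they move widely with the assumed shift.

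A second reply is that the rating analysis is already confined to the intervention arm, so what it will compute is close to what is asked for here. This also stands. For the rating, only the label and the causal wording need to change.

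A third is that weighing adherence uses the same definition in both arms. That is fair for the definition, though not for the data source, and it does not help the overall score or make adherence a pre-randomisation variable.

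Finally, these are process-evaluation analyses in a proof-of-concept trial. The strengths list ties future improvement to liking, usage and perceived effectiveness, and does not mention moderator analyses, so the stakes should not be overstated.

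None of this rescues adherence or the rating as moderators. An analysis plan can add a term to a model. It cannot make an end-of-programme, one-arm rating modify a randomised comparison.

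**Conclusion.** The point holds in two parts of unequal strength. Listing adherence and the overall rating as moderators of effectiveness is wrong as written, whatever the analysis plan contains. Their associations with weight change may be described but do not show for whom the intervention works. For education and baseline liking of weighing, the point is conditional: as worded, the analysis estimates a prognostic effect, which does not meet the stated aim unless a condition-by-variable interaction is fitted.

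The size of the first part is not numerical; it is a matter of what can be concluded. For the second, the firm figure is the limited information available. On the assumptions of 80 completers, SD 2.13 kg and an even binary split, the smallest interaction detectable with 80% power is about 2.7 kg, well above the 1.5 kg main effect for which the trial is sized. An uneven split would make this worse. The primary analysis and the sample size are not affected.

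**What to change.** 1. Take adherence and the overall rating off the list of moderators in both sections. Report them as associations with weight change within the intervention arm, with no claim of effect or moderation, and note that reverse causation and confounding cannot be excluded. The planned comparison of adherence rates between arms can stay as it is.
2. For highest educational qualification and baseline liking of weighing, state that moderation is tested by adding the variable and its product with condition to the primary regression (8-week weight on condition, baseline weight and practice). Report the interaction with its 95% confidence interval, labelled exploratory. If the analysis plan already says this, align the article's wording with it.
3. Say openly that power for these interactions is low, so that a non-significant result is not read as evidence of no moderation.

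The cost is a change of wording and of the secondary analysis. No new data, visits or participants are needed. The real downside is that the interaction estimates will be imprecise.
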